## 5. ANALYSIS

### 5.1. Outcome definitions

Any suspected cardiovascular event suggestive of an endpoint as well as all deaths were submitted to the blind independent Clinical Events Committee (CEC). The CEC reviewed the data of the reported cases in a blinded manner for adjudication purpose and validate if the event should be considered as an endpoint. Cardiovascular and respiratory events adjudicated and validated by the CEC will be used for the analyses.

Events that the CEC could not classify as well as suspected event according to investigator but not confirmed by the CEC will not be part of the outcomes. defined in study protocol, the following outcomes will be evaluated:

**Primary efficacy outcome:** A hierarchical outcome consisting of all-cause death, myocardial infarction (MI), stroke, unstable angina, hospitalization for heart failure, urgent coronary revascularization or hospitalization for respiratory infection (excluding COVID-19).

**Key secondary outcome:** A hierarchical outcome consisting of CV death, MI, or stroke.

**Secondary efficacy outcomes:**

The first occurrence of the following endpoints:

- Total mortality
- CV mortality
- Myocardial infarction
- Stroke
- Hospitalization for unstable angina
- Need for myocardial revascularization (urgent and non-urgent)
- Hospitalization for heart failure
- TIA (Transient ischemic attack)
- Hospitalization for respiratory infections (including COVID-19)
- Hospitalization for respiratory infections (excluding COVID-19)
- Hospitalization for COVID-19

[figure not shown]

- Stent thrombosis

Additionally, the primary efficacy outcome with events truncated at 45 days after randomization (i.e., the period of maximum exposure for the intervention group) will also be analyzed.

#### Safety outcomes:

- Number and percent of unexpected serious adverse events (event that presents immediate risk to life, persistent or significant disability, requiring or prolonging the hospitalization, resulting in congenital anomaly, Guillian Barré syndrome, anaphylactic vaccination reaction, Peripheral Facial Paralysis, encephalitis or myelitis, optic neuritis, Stevens-Johnson syndrome, toxic epidermal necrolysis, anaphylactic vaccination reaction, another unexpected event judged as serious).
- Local and systemic adverse events after vaccination.
- Use of other vaccine than those available in the study (Hepatitis, Trivalent Influenza (Government), Pneumococcal, Yellow fever, Viral triple, DPT Adult, HPV).

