## 4.3 Exploratory endpoints

Occurrence of local and systemic adverse events at 7 and 28 days after vaccination. Occurrence of serious adverse events related to vaccination and serious adverse events within 12 months; Occurrence of the primary endpoint between treatment groups within 45 days of randomization; Vaccine antigen responses  $\geq 4$  times baseline by hemagglutination inhibition test.

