## **(II) Systemic adverse events**

These are benign and self-limited, such as fever, malaise, myalgia, hypersensitivity (anaphylactic) reactions and neurological manifestations (narcolepsy and Guillain-Barré syndrome, even without a cause-effect definition). These manifestations are more frequent in people who have not had previous contact with vaccine antigens.

Anaphylactic reactions (hypersensitivity type I) are extremely rare and can be related to any component of the vaccine. Some influenza vaccines may contain minimal amounts of egg protein, which may induce immediate allergic reactions in individuals with severe allergy to this protein. These events may be seen more frequently in individuals who have never had contact with the influenza vaccine. Fever will be classified into two groups by thermometer measurements: Fever condition will be classified when the mean body temperature presents values above 37.5 °C. Severe fever when the temperature is above 38.9 °C with or without hospitalization.

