### **5.1 Serious adverse event (SAE)**

Results (defined above) that meet the criteria for a SAE will not be reported as a SAE, but as outcomes. A SAE is defined as any AE that results in death, is immediately life-threatening, results in persistent or significant deficiency/disability, requires or prolongates the patient's hospitalization, is a congenital anomaly/birth defect, or should be considered serious by any other reason if it is an important medical event when based on proper medical judgment that could jeopardize the patient and may require medical or surgical intervention to prevent one of the other outcomes listed in the definitions above.

The intensity of the AE should be judged based on the following:

- Mild: Awareness of signs or symptoms that are easily tolerated
- Moderate: Sufficient discomfort to cause interference with usual activity
- Severe: Disabling or causing inability to work or perform usual activities.

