### **5.2 Causal relation of the adverse event**

Medical judgment should be used to determine the relation, considering all relevant factors, including reaction pattern, temporal relation, withdrawal or reintroduction of study drug. Only unexpected and previously unreported serious adverse events believed to have a reasonable level of certainty to be related to study medication need to be immediately reported (i.e., within 24 hours of awareness of the event) to the VIP-ACS Project Office. For such events, the research team must complete a SAE CRF and immediately enter it into the e-CRF. The VIP-ACS Project Office will then

inform ANVISA (Brazilian Health Surveillance Agency) in a timely manner in accordance with the SAE Management Plan.

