### **5.4 Treatment of adverse events**

The treatment of any adverse event will be as identified by local investigators and based on Good Clinical Practice. The identification and therapies adopted must be described in the field specific o vaccination safety and/or in the field of Serious Adverse Events contained in the eCRF. If a serious adverse event occurs, the Study Coordinating Site must be informed.

All concomitant medications, except for vitamins and dietary supplements, must be described in the Booklet and reported in the eCRF. The use of medications for prophylaxis or control of febrile conditions must be included in the eCRF.

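### The SAP limits its serious-adverse-event outcome to an undefined class of 'unexpected' events with no time window, where protocol 4.3 lists vaccine-related SAEs and SAEs within 12 months

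*Combined protocol and SAP*

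**What the plan says.** **Protocol.** Section 4.3 (Exploratory endpoints) includes "Occurrence of serious adverse events related to vaccination and serious adverse events within 12 months". Section 5.1 defines an SAE in general terms and sets trial endpoints aside: "Results (defined above) that meet the criteria for a SAE will not be reported as a SAE, but as outcomes". Within section 5, the word unexpected helps decide which SAEs go to the project office within 24 hours (5.2) and which are reported to local authorities and ethics committees (5.3). Section 3.4 makes allocation open to investigators, care team and patients.

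**SAP.** Section 5.1 (Safety outcomes) gives the SAE outcome as "Number and percent of unexpected serious adverse events (event that presents immediate risk to life". The list that follows names specific reactions, among them "Guillian Barré syndrome, anaphylactic vaccination reaction, Peripheral Facial Paralysis", and ends with "another unexpected event judged as serious". No time window is given and vaccine-related events are not separated. Section 5.2 describes local and systemic adverse events by group to day 7, counts patients with any vaccination adverse event with a 95% CI, and lists all adverse events by patient. It has no sentence on SAEs. Section 5.7 analyses SAEs that are possible trial endpoints with the efficacy methods.

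**The concern.** The protocol and the SAP describe different serious-harm outcomes. A word that the protocol uses to trigger reporting has become part of an outcome definition in the SAP. If it is applied literally, what reaches the SAE table depends on a label that neither document defines.

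This matters for two reasons. The rate of adverse events related to the double dose is a stated, exploratory, objective (protocol 2.3). And the trial is open label: the blinded committee described in SAP 5.1 receives suspected endpoint events and deaths, and no blinded review of expectedness is described. A narrower count is less informative, and a label applied differently in the two arms could raise or lower the apparent ratio.

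**Working it through.** **1. Passages side by side**

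| Feature | Protocol 4.3 | SAP 5.1 |
|---|---|---|
| Expectedness filter | None | Yes, in the opening words and again in the catch-all item |
| Time window | 12 months | None stated |
| Vaccine-related SAEs separately | Yes | No |
| Definition of unexpected | Not needed | None; no reference list or assessor named |

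**2. Does other SAP text restore the protocol's endpoints?**

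- SAP 5.7 covers only SAEs that are possible trial endpoints.
- The by-group description in SAP 5.2 concerns local and systemic events to day 7. Its count of any vaccination adverse event does not separate serious events. The listing is by patient and makes no comparison.
- The SAP summary of changes mentions no change to the SAE outcome, so it gives no reason for the narrowing.

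What remains without a summary by arm is the set of SAEs that are (a) not trial endpoints, (b) not named in SAP 5.1 and (c) not labelled unexpected.

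**3. Illustration of size**

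The documents give no SAE rate and no SAE power, so there is no figure of theirs to reproduce. Only n = 900 per arm comes from them (SAP 2.3). Assumed: a control risk p of non-endpoint SAEs of 3%, 5% or 10%; a true risk ratio of 1.5; and a share u labelled unexpected, equal in both arms.

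With p1 = p·u, p2 = 1.5·p·u and p̄ their mean, for a two-sided 5% test:

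power = Φ{ [ (p2 − p1) − 1.96·√(2p̄(1−p̄)/n) ] / √[ (p1(1−p1) + p2(1−p2))/n ] }

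For p = 5% and u = 1: p1 = 0.05, p2 = 0.075, p̄ = 0.0625. The null SE is 0.01141 and the alternative SE is 0.01140, so power = Φ[(0.025 − 0.02237)/0.01140] = Φ(0.23) = 59%.

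| Control SAE risk | All counted (u = 1) | Half labelled (u = 0.5) | Quarter labelled (u = 0.25) |
|---|---|---|---|
| 3% | 39% | 22% | 13% |
| 5% | 59% | 33% | 19% |
| 10% | 89% | 59% | 33% |

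If the share differs by arm, observed ratio = true ratio × (share in double dose ÷ share in control):

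- 33.3% against 50%: a true 1.5 appears as 1.5 × 0.333/0.5 = 1.0, and a true 1.0 appears as 0.67.
- 60% against 50%: a true 1.0 appears as 1.2.
- Equal shares: the ratio is unchanged and only precision is lost.

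**The case against.** The best reply is that the SAP list reads much like a general SAE definition, so unexpected may be loose wording and not a deliberate filter. The outcome is also exploratory in the protocol and descriptive in the SAP: a number and percent, with no SAE ratio or test planned, so the power figures concern an analysis that nobody has promised. Both points stand and limit the weight of the issue. They do not remove it, because the missing window and the missing vaccine-related count remain even if the word is loose.

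A reader might infer more than the documents support:

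- *The SAP omits expected serious harm.* Too broad. Guillain-Barré syndrome, anaphylaxis and other reactions are counted by name, and endpoint-type SAEs are compared under SAP 5.7.
- *Leaving death out of the SAP list is an error.* It is consistent with protocol 5.1. All-cause death leads the primary outcome, and every death goes to the blinded committee.
- *Unblinded site staff decide what is unexpected.* No text says who decides. Open allocation and the committee's scope make this a fair inference, not a stated fact.
- *A bleeding or arrhythmia admission would be missed.* This needs a meaning of expected that the documents do not give. Neither event is among the vaccine reactions they list, so such an admission could well be counted as unexpected.
- *The documents disagree on which reactions are expected.* Protocol 4.4.10 introduces the systemic reactions with "These are benign and self-limited, such as fever, malaise, myalgia, hypersensitivity (anaphylactic) reactions and neurological manifestations". That description fits anaphylaxis and Guillain-Barré syndrome poorly, but it does not call them expected, and the SAP counts both.
- *Other SAEs are never collected.* Protocol 5.2 limits what must be reported within 24 hours, and "For such events, the research team must complete a SAE CRF" refers to those events. Section 5.4 adds "If a serious adverse event occurs, the Study Coordinating Site must be informed" and refers to an SAE field in the eCRF.

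**Conclusion.** The mismatch is real and should be settled before analysis. Following SAP 5.1 literally would give a different and narrower SAE table than protocol 4.3 calls for, and it would rest on an undefined label in an open-label trial. What is lost is the by-arm summary of non-endpoint SAEs that are neither labelled unexpected nor named in the list, together with the 12-month window and the separate count of vaccine-related SAEs.

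The size cannot be estimated from the documents. The illustration shows direction only: equal labelling lowers precision, and unequal labelling distorts the ratio either way. Nothing shows that unequal labelling would occur. The efficacy analyses, the handling of deaths and the named vaccine reactions are unaffected.

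**What to change.** In SAP 5.1 and 5.2, replace the SAE outcome with two counts taken from protocol 4.3, each as number and percent of patients by arm:

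1. Any SAE that is not a trial endpoint, to 12 months, with the starting point of the window stated.
2. Any vaccine-related SAE.

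Use the populations that SAP 3.3 already sets: the Safety population by vaccine received, with ITT as the sensitivity analysis. Keep unexpected SAEs only as a subset, judged against a reference list named in the SAP and, where judgement is needed, by an assessor blinded to arm. The named reactions can stay as separate lines.

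The cost is SAP wording and one or two tables. The protocol already requires SAEs to be notified to the coordinating site and refers to an eCRF field for them, so no new form is needed. Blinded classification of the subset would add a small amount of review work.

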## **5.2. Analysis methods**

Primary efficacy outcome: The analysis of primary efficacy endpoint—a hierarchical outcome consisting of all-cause death, MI, stroke, hospitalization for unstable angina, hospitalization for heart failure, urgent coronary revascularization or hospitalization for respiratory infection (excluding COVID-19) will be the comparison between the two arms using the unmatched win ratio method (refer to section 2.3).

Secondary key efficacy outcome: The secondary key outcome is defined also as a hierarchical outcome of CV death, MI, or stroke, in that order, and will be compared with the Win Ratio statistic using the same definitions for the primary endpoint.

Secondary efficacy outcomes: The analysis of the secondary efficacy endpoints, defined as time to first event of: All-cause mortality, Mortality from cardiovascular causes, Myocardial infarction, Stroke, Hospitalization for unstable angina, Need for myocardial revascularization (urgent and non-urgent), Hospitalization for heart failure, TIA (Transient ischemic attack), Hospitalization for respiratory and pulmonary infections, Hospitalization for COVID-19, and Stent thrombosis; will be tested using Cox proportional hazard models. All the effects statistic

[figure not shown]

will be Hazard Ratio (HR) between the two arms within 12 months, and corresponding 95%CI will be provided. Underlying assumptions of the Cox Proportional Hazard Model will be checked using graphical methods

The estimates of time to the first event (median time of event-free) will be also computed if possible, and Kaplan-Meier curves will be displayed, by treatment arm. Additional efficacy outcomes (Influenza season in the southern hemisphere): the prevalence of each strain within of the subtypes circulating in each season and location will be described in tables using proportions and graphically. The proportions will be compared using comparison of proportions tests.

Safety Outcomes: The number of patients having local and systemic adverse events up to 7 days after vaccination will be described by group and overall. The number of patients having any vaccination adverse event will be computed, and the 95% CI will be presented.

All the adverse events will be listed, by patient.

### **5.3. Sensitivity analyses:**

A sensitivity analysis will be performed for the primary efficacy outcome including also hospitalizations for respiratory infections due to COVID-19.

Additionally, the primary and key secondary combined outcomes will also be evaluated by survival Cox proportional hazard models considering the first occurrence of any of the events listed. This approach does not define any hierarchy among the events.

### **5.4. Multiplicity adjustments**

In order to keep the trial wise type I error, a closed test hierarchical approach will be used for adjustment for multiple hypothesis. If a difference at a significance level of 0.05 is found after a non-significant p-value, that test will be declared only nominally significant, and any further finding in the hierarchical sequence will be deemed as only exploratory. First, the primary outcome will be tested, followed by the key secondary outcome, then the following secondary outcomes, in this respective order: all-cause mortality, mortality from cardiovascular causes, myocardial infarction, stroke, hospitalization for unstable angina, need for myocardial revascularization (urgent and non-urgent), hospitalization for heart failure, TIA (transient ischemic attack), hospitalization for respiratory and pulmonary infections, hospitalization for covid-19, and stent

[figure not shown]

thrombosis. For this framework, both primary and key secondary outcomes will be analyzed by the Win Ratio method, while the other secondary outcomes will be analyzed by the Cox proportional hazard models with HR and 95% CI.

### **5.5 Subgroup analyses:**

As many of the baseline characteristics are known to be prognostic for the clinical outcomes in the study population with high-risk cardiovascular disease (as sex, age group, race/ethnicity, smoking status, etc.), internal consistency of the primary analysis will be assessed in subgroups defined by these and other baseline characteristics.

Heterogeneity of efficacy will be assessed using interaction tests of treatment by each of these baseline covariates and by influenza season (Period), using the same aforementioned models.

The following subgroups will be prespecified in this SAP:

- Male vs. females;
- Age  $\geq$  vs. < 60 years;
- ACS presentation: (STEMI, NSTEMI, unstable angina)
- Diabetes vs. no diabetes;
- Smokers vs, non-smokers
- White race vs. non-white
- Killip class 2 or more vs. Killip class 1
- Previous heart failure vs not;
- Previous MI vs not;
- Previous stroke vs. not;
- Previous PCI vs not;
- Previous CABG vs not;
- History of chronic lung disease vs not;
- Prior COVID-19 vs.not.

[figure not shown]

- Time from presenting ACS to randomization (in tertiles)
- Time from hospitalization to randomization (in tertiles)
- Influenza season (Mar-Jul vs. other months);
- Enrollment year (2019 vs. 2020);
- Regions of the country (North and Northeastern vs others)
- COVID-19 vaccination vs not-vaccination.

## 5.5. Missing data

For categorical variables, patients with missing data will not be included in calculations of percentages, unless otherwise specified. When relevant, the number of patients with missing data will be presented.

All missing or partial data will be presented in the subject data listing as they are recorded on the CRF including best estimate dates of site investigators (see below) collected in the clinical database. All efforts will be made to collect complete data for all subjects randomized in this study.

### ***Missing or incomplete event dates***

All time variables, such as age, time to/from event or duration, will be calculated as: Date 2 (Final) – Date 1 (Initial) + 1. If the variable is calculated in months, the time in days will be divided by 30.44; if in years, the time will be divided by 365.25.

When an event date is unknown, the site investigator will be asked to provide a best estimate as to when the event may have occurred. Even though the exact date of an event is unknown, the investigator often does know some information that would indicate the approximate date, such as the first week of a month, in the fall of a year, or the middle of a particular year, or at least the date when the subject was last seen or contacted. This information can be meaningfully incorporated into the estimated date recorded, as this is likely to be closer to the true date than any produced by an uninformed computer program. This estimated date should be the middle date within the period that the event is known to have occurred. If the event is known to have occurred in the first week of a month, then the date in the middle of that week should be recorded as the estimate. If it occurred in the fall of a year, then the

[figure not shown]

middle date in the fall is the appropriate estimate. If no information is known then the date in the middle of the plausible time period should be given, based on the last contact with the subject prior to the event and the date of contact when information about the event was known. This method for date estimation has been used in many studies and is recommended by Dubois and Hebert (2001) .

If the site investigator does not provide a best estimate as to when the event occurred, the study team will follow the above rules to estimate the event date. If the date/time information is not sufficient to determine whether an event occurred prior or after randomization, the event is considered as an outcome, to be conservative. The event start date will be imputed no earlier than randomization date.

### ***Missing data related of unobserved follow-up time up until the timing of final analysis***

Unobserved follow-up time may occur due to subjects who are non-compliant with study follow-up, for example due to loss of follow-up or premature complete withdrawal of informed consent. Subjects censored administratively at the end of follow-up period or censored at time of non-CV death (in the case of the key secondary outcome) are not contributing missing follow-up time.

Missing data due to follow-up non-completion before experiencing a primary efficacy outcome event will be addressed by assuming that the data is missing at random (MAR assumption).

The sensitivity analysis of the potential impact of missing data on the primary efficacy outcome follows the elements described by Little et. al. (2016), and involves two steps:

1. A descriptive comparison of key baseline characteristics and post-randomization events preceding the end of follow-up to assess whether subjects with missing data differ systematically from subjects who complete the follow-up.
2. A pattern mixture model using multiple imputation techniques to investigate the potential impact of missing data on the primary efficacy analysis if non-ignorable censoring is assumed to be differential.

In addition, the extent of missing data will be described by the fraction of subjects with unobserved follow-up time and the fraction of unobserved follow-up subject-years.

[figure not shown]

All analyses of the potential impact of missing data will be performed in the ITT analysis set.

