##### *I. Death from lung disease*

It refers to all death as a direct consequence of respiratory failure caused by a primary disease of the lung parenchyma, whether infectious or not. Excludes cases of death from pulmonary embolism or cardiogenic pulmonary edema (situations that will be considered as CV deaths).

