In this sense, and based on the results of the aforementioned meta-analysis, non-controllable factors (COVID-19) and the findings of the IAMI trial, we recalculated the VIP-ACS sample size using a statistical Win Ratio (WR) approach, for analysis of efficacy of the double-dose influenza vaccine compared to the standard dose vaccine, in which it was estimated that the inclusion of 1800 patients (900 per group) for a WR of 1.41 with a power of 82.6% and an alpha of 5 %. These data were obtained over 10,000 simulations, considering the following event rates in the control group: death, 7.0%; AMI, 3.4%; stroke, 1.0%; hospitalization for unstable angina, 2.7%; hospitalization for heart failure, 2.9%; emergency revascularization, 1.0% and hospitalization for respiratory infections, 1.0%, and assuming a reduction of these events with double-dose vaccine in: death by 2.0%; AMI by 0.9%; Stroke by 0.3%; Hospitalization for unstable

angina by 0.8%; Hospitalization for heart failure by 0.7%; Emergency coronary revascularization by 0.2% and Hospitalizations for respiratory infections by 0.3%.

Considering that the primary endpoint of the VIP-ACS comprises more individual endpoints than the IAMI trial, and from the meta-analysis studies, the sample size calculation proposed to the VIP-ACS to assess possible reductions in hierarchical events of the primary endpoint is comprehensive and conservative to the purpose of the study, and overcomes the external conditions involved in the COVID-19 pandemic.

The analysis of the primary endpoint will exclude hospitalizations for respiratory causes caused by COVID-19. To this end, a sensitivity analysis and other exploratory analysis of the impact of COVID-19 on VIP-ACS events are planned.

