### 2.3. Sample Size and Statistical Framework

The sample size calculations were based on the primary efficacy outcome, that is, the hierarchical analysis time to of all-cause death, myocardial infarction, stroke, unstable angina, hospitalization for heart failure, urgent coronary revascularization and hospitalization for respiratory infection (excluding COVID-19), using the win ratio methodErro! Fonte de referência não encontrada.. In the win ratio method, every patient from the intervention group will be compared against every patient from the control group. Among each unique patient pair, the “loser” will be the first patient who presents an outcome, according to a predefined hierarchy. For example, if patient X dies and patient Y is alive by the end of follow-up, patient Y will be considered the “winner” in that match. If both participants die during the study, the “winner” will be the participant with the longest time alive since randomization. In case the patients remain tied – if neither dies by the end of 12 months or if both die with the same follow-up time – the next item in the hierarchy, myocardial infarction, will be analyzed in the same

[figure not shown]

manner (presence vs. absence of event and, if both presented the outcome, time to first event). If the patient pair remains tied, the analysis will be proceeded similarly for each component of primary outcome in the hierarchy. A tie will be declared if participants remain tied after the final item, hospitalization for respiratory infection. This will happen if neither patient presents an outcome or if they present the same outcomes for the first time at the same follow-up times. Participants will be censored at the 12-month follow-up; if the follow-up time for any participant is censored before this time due to any reason, comparisons with this individual will be made only until the moment of censorship.

The win ratio method will be analyzed as the following:

H0:  $\Psi=1$  (win ratio = 1): the ratio of all winners in the intervention group by all winners in the control group is equal to 1.

H1:  $\Psi \neq 1$  (win ratio  $\neq 1$ ): the ratio of all winners in the intervention group by all winners in the control group is not 1.

The win ratio statistic is defined as the ratio of wins ( $N_w$ : Number of Wins of the intervention group,  $N_L$ : Number of Losses of the intervention group) in each group (intervention vs. control).

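### Non-CV deaths are censored in the key secondary win ratio, and no competing-risk method is planned for the component outcomes; the gap is small and two supportive analyses close it

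*Combined protocol and SAP*

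**What the plan says.** SAP 5.1 defines the key secondary outcome as "A hierarchical outcome consisting of CV death, MI, or stroke". SAP 5.2 adds that it "will be compared with the Win Ratio statistic using the same definitions for the primary endpoint", so the scoring rules of SAP 2.3 apply. Those rules say that if a patient's follow-up is censored before 12 months for whatever reason, "comparisons with this individual will be made only until the moment of censorship".

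SAP 5.5 (Missing data, unobserved follow-up time) says that patients "censored at time of non-CV death (in the case of the key secondary outcome) are not contributing missing follow-up time". Protocol 4.4.4.2 places death from lung disease among the non-cardiovascular deaths: "It refers to all death as a direct consequence of respiratory failure caused by a primary disease of the lung parenchyma", whether infectious or not. A fatal pneumonia is therefore non-CV.

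The remaining secondary outcomes "will be tested using Cox proportional hazard models", and "Kaplan-Meier curves will be displayed, by treatment arm" (SAP 5.2). Protocol 6.2 also plans Kaplan-Meier for the primary endpoint and a similar analysis for secondary endpoints. Neither document names a competing-risk method or a cumulative incidence function.

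**The concern.** The key secondary is the second test in the confirmatory sequence (SAP 5.4). Once a non-CV death is censored, each of that patient's pairs is decided only on what happened before the death. The opponent's later CV deaths, MIs and strokes drop out, and survival itself earns the opponent nothing. In an influenza-vaccine trial, respiratory death is a plausible place for the effects on CV and non-CV death to part, and no planned analysis shows how far the key secondary result depends on this scoring.

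The second part is descriptive. A patient who has died can no longer have an MI or a heart failure admission. Censoring at death treats that patient as still at risk, so a risk read from 1-minus-Kaplan-Meier is too high.

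**Working it through.** **Inputs.** Protocol 6.1 gives 12-month control rates of "death, 7.0%; AMI, 3.4%; stroke, 1.0" per cent; SAP 2.3 agrees. SAP 2.3 also supplies the 28% relative reduction, independent events, exponential times and 900 patients per arm. The CV share of deaths is not stated. I assume 50-80%, that is, 20-50% non-CV.

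**The plan's own figure.** The documents give no tie share and no Kaplan-Meier bias to reproduce. As a check on the pairwise scoring, the SAP's seven component rates and reductions return a win ratio of 1.41, the protocol's figure. Simulated power was 79.6-80.0% against the stated 82.6%. That difference concerns the primary outcome and has no bearing here.

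**1. How a non-CV death is scored.** Take a patient who dies of pneumonia at time t (in years) with no earlier MI or stroke. The pair ties if the opponent has had no CV death, MI or stroke by t:

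P(tie) = [(1 - p_CV)(1 - p_MI)(1 - p_stroke)]^t

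With 70% of deaths CV, p_CV = 0.7 × 7.0% = 4.9%. Against a control opponent:
- t = 1: 0.951 × 0.966 × 0.990 = 0.909
- t = 0.5: √0.909 = 0.954
- t = 0.25: 0.977

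A pairwise simulation that includes the patient's own earlier MI or stroke gives:

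| Patient and rule | Ties | Wins | Losses |
|---|---|---|---|
| Non-CV death, SAP rule (CV share 50-80%) | 94-95% | 3-4% | about 2% |
| Non-CV death, any death in tier 1 | about 0% | about 3% | about 97% |
| Event-free survivor (CV share 70%) | 91-93% | 7-9% | 0% |

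The survivor row is the same formula at t = 1: 0.909 against control and 0.934 against double-dose opponents. The remainder are wins.

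**2. How many pairs are involved.** A pair is affected if either patient dies of a non-CV cause. With the 28% reduction applied to these deaths:
- 20% non-CV: 1 - (1 - 0.014)(1 - 0.72 × 0.014) = 2.4%
- 50% non-CV: 1 - (1 - 0.035)(1 - 0.72 × 0.035) = 5.9%

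**3. Effect on the win ratio.** By simulation at 900 per arm:

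| Assumed effect | SAP rule | Any death in tier 1 |
|---|---|---|
| 28% reduction throughout, 20-50% of deaths non-CV | 1.41 | 1.41-1.42 |
| CV events down 28%, non-CV deaths up 30% (40% non-CV) | 1.40 | 1.16 |
| No effect on CV events, non-CV deaths down 60% (40% non-CV) | 1.00 | 1.19 |

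The last two rows are illustrations; the documents predict neither.

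**4. Kaplan-Meier against cumulative incidence.** With constant hazards λ = -ln(1 - p), the Aalen-Johansen risk at 12 months is

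F = λ_e / (λ_e + λ_d) × [1 - (1 - p_e)(1 - p_d)]

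For MI with 7% deaths:
- λ_e = -ln(0.966) = 0.03459 and λ_d = -ln(0.93) = 0.07257
- F = 0.03459 / 0.10716 × (1 - 0.966 × 0.93) = 0.3228 × 0.1016 = 3.28%
- 1-minus-Kaplan-Meier gives 3.40%, which is 0.12 points or about 3.7% too high in relative terms

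The same relative figure applies to heart failure (2.90% against 2.80%) and respiratory hospitalization (1.00% against 0.96%). Across the non-fatal components the gap is 0.02-0.12 points. At 5% mortality (7.0% less the planned 2.0 points) it is about 2.6% relative. If every death fell on day 0 the bound would be 1/0.93 - 1 = 7.5%.

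**5. CV death.** Only non-CV death competes with it:
- 20% non-CV: p_e = 5.6%, p_d = 1.4%, F = 5.56%, overstatement 0.7%
- 50% non-CV: p_e = p_d = 3.5%, F = 3.44%, overstatement 1.8%

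**The case against.** The strongest reply is that a CV-specific endpoint is meant to ignore non-CV death, and that censoring at other deaths is the usual cause-specific approach. That stands. So does the SAP 5.5 sentence. A reader might take it for a leftover error from the first-event analysis, but no CV event can follow a death, so it is right that no follow-up is missing.

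Two stronger readings of the win ratio are tempting and fail.
- A reader might treat the high tie share as the flaw. Events are rare, and event-free survivors tie almost as often. What matters is that a pneumonia death wins slightly more often than it loses.
- A reader might infer that censoring costs power, because a version with all-cause death in tier 1 has more. That version is a different endpoint with more events, and the gain assumes the same 28% effect on non-CV death. With equal effects the win ratio is the same.

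The plan also covers much of the ground already. The primary outcome has all-cause death in its first tier, SAP 5.4 tests all-cause and CV mortality directly after the key secondary, and SAP 5.6 adds composites with all-cause death and with pulmonary or infectious death. None of these is the key secondary hierarchy with all deaths counted, so one narrow comparison is missing.

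On Kaplan-Meier, a reader might conclude that the reported 12-month component risks will be biased. The SAP promises hazard ratios, median event-free time where possible, and displayed curves; it does not say that 1-minus-Kaplan-Meier will be reported as a risk. Censoring at death is explicit only for the key secondary and is the default reading elsewhere. The planning rates are reported event rates, used here only to size the effect.

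**Conclusion.** The point holds as a minor, inexpensive improvement. No confirmatory test is invalid, and the Cox hazard ratios remain valid as cause-specific hazard ratios.

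The key secondary scores a non-CV death about like event-free survival. This affects 2.4-5.9% of pairs if 20-50% of deaths are non-CV. It leaves the win ratio almost unchanged if the effects on CV and non-CV death are equal, and can hide benefit or harm if they differ.

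If death is censored for the non-fatal outcomes, risks read from the Kaplan-Meier curves are too high by about 3.7% relative (0.02-0.12 points) at 7% mortality and constant hazards, and by about 0.7-1.8% for CV death. The direction is certain; the size rests on the planned rates and on the assumed split and timing of deaths.

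**What to change.** 1. In SAP 5.2, display Aalen-Johansen cumulative incidence instead of Kaplan-Meier for every outcome that does not include all-cause death, with death outside the endpoint as the competing event. Keep the Cox model and label its result a cause-specific hazard ratio.
2. In SAP 5.3, add a supportive key secondary win ratio with all-cause death in the first tier, then MI, then stroke. Report by arm the number of key secondary pairs cut short by a non-CV death.

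The cost is a few lines of SAP text and of code, using deaths that the Clinical Events Committee already adjudicates. The confirmatory definition, the test order and alpha stay as they are. Displayed non-fatal component risks would fall by roughly 0.02-0.12 percentage points.
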